#### Missing data and adherence

Participants missing ≥ 10% of required sleep intervention nights (defined as < 22 nights of wearing the sleep intervention over the 8-week intervention period) will be flagged for sensitivity analyses. If a participant misses > 2 consecutive weeks of data and/or fails to complete either of the full-length, digital cognitive assessments, such participants will be excluded from per-protocol analyses but retained in intention-to-treat models. Multiple imputations will not be applied due to the small sample size; instead, pattern mixture modeling or last observation carried forward (LOCF) methods will be used where applicable.

Adherence to the recommended neuromodulation utilization for the sleep intervention will be monitored via the Elemind application, which will log device usage and track sleep metrics. In addition, weekly phone or video check-ins (10–15 minutes) will be made to monitor engagement, support adherence, and troubleshoot technical issues. All reports of adherence will be documented upon the completion of each call/video check-in.

#### Limitations

This study will not include a sham stimulation control for the sleep-only group. The decision to forgo a sham condition reflects the real-world, comparative effectiveness design of the CASE study and prioritizes ecological validity over internal blinding. Nonetheless, the absence of participant blinding may introduce potential placebo effects. To address this analytically, expectancy-related influences will be modeled using self-reported perceived benefit measures as an additional covariate in the regression models. Sensitivity analyses will explore whether high expectancy ratings moderate intervention effects. Between-arm comparisons will further contextualize the potential role of non-specific treatment effects in observed outcomes.

In addition, the 8-week interventional period of this clinical trial may not be a sufficient timeframe for detecting significant changes in brain biomarkers; nonetheless, it should be emphasized that the predominant goal of this pilot trial is to identify early trends and signals in these aforestated biomarkers, which will, in turn, inform the design of future, longer-term, fully powered trials. Furthermore, this exploratory approach will enable the assessment of the feasibility and potential effects of each intervention in a relatively small cohort and prefaces more extensive future studies. Notably, the 8-week interventional trial duration was selected based on prior study findings, which showed that behavioral interventions have the capacity to result in early changes in cognitive and physiological measures within a relatively short timeframe [40, 41].

#### Temporal synchronization

All data sources—including Elemind (sleep), Lys (light exposure), Fitbit (physical activity/exercise), and digital cognitive assessments (cognitive function)—will be time-stamped and aligned using a centralized database. Sampling frames will be linked to specific intervention events and assessment windows to enable a temporally precise integration of cognitive and sleep data streams. By integrating wearable neurotechnology, frequent cognitive assessments, and remote monitoring within a structured intervention framework, this arm of the CASE study aims to evaluate the adherence and early efficacy signals of at-home sleep neuromodulation in aging adults.

### Interventional group 3 (combined sleep and exercise)

Participants randomized to the combined intervention group will engage in both structured exercise sessions and sleep neuromodulation over an 8-week study period. This arm is designed to explore the additive and potentially synergistic effects of engaging in both interventions concurrently while assessing adherence and participant burden, which will, in turn, inform future multimodal approaches to cognitive aging and AD prevention.

#### Protocol structure and considerations

To reduce participant burden and improve standardization, in-lab exercise sessions and cognitive assessments will follow the same cadence and structure as in the exercise-only arm: twice-weekly, 60-minute, supervised sessions that will focus on aerobic and resistance training, home-based walking program, and brief digital cognitive assessments (the Digital Neuro-Signature Platform) immediately after each session. Participants will also wear the Elemind Neuromodulation headband for at least 3–4 nights per week across the 8-week period, with an initial 7-day, passive, onboarding screening phase of wearing the headband nightly without stimulation in combination with wearing the Fitbit device continuously to establish baseline sleep patterns, physical activity levels, and ensure that all eligibility criteria are satisfied. Finally, subjects will also wear the Lys device continuously throughout the 8-week trial period.

To manage cumulative burden, scheduling flexibility will be emphasized. Although participants will be offered a choice of days and times for in-lab sessions to fit each participant’s weekly routines, morning times will be strongly encouraged across all participants, as prior work has suggested that older adults generally show better cognitive and exercise performance in the mornings [42, 43]; this will further improve standardization. Staff will work closely with participants to accommodate visit times and ensure ample time for recovery between activities. Weekly adherence and well-being check-ins will be conducted and documented to monitor fatigue, motivation, and adverse effects.

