#### Adherence and engagement

In order to assess adherence to the exercise sessions, attendance will be recorded for all in-person sessions, and wearable devices (Fitbit) will track daily physical activity, including steps, heart rate, and durations of physical activity. Weekly check-ins (10–15 minutes) via phone or secure teleconference will be conducted and documented to ensure protocol adherence, troubleshoot technical issues, and maintain engagement. All data will be stored in HIPAA-compliant systems. Fitbit and the Digital Neuro-Signature Platform data will be de-identified and linked using secure participant codes. Statistical models will include age, sex, years of educational attainment, employment status (unemployed/employed), socioeconomic status, baseline sleep metrics, baseline physical activity levels, and cognitive status as covariates. By integrating standardized, in-lab exercises, wearable technology, digital cognitive assessments, and multimodal biomarker data, this arm of the *CASE* study aims to explore the cognitive, brain, and cardiometabolic impacts induced by structured exercise in aging adults who are at higher risk for AD using a real-world, ecologically valid framework.

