### Data and safety monitoring plan

Clinical site monitoring is a vital process that ensures the safety and well-being of human subjects participating in a clinical trial. Clinical site monitoring will be conducted to ensure that the reported trial data is accurate, complete, and verifiable. Site monitoring will also ensure that the trial is in full compliance with the approved protocol/amendment(s), Good Clinical Practices, and applicable regulatory requirements. During the study, a medical doctor will monitor participants who report experiencing medical issues. Should any medical issues arise, participants will be encouraged to seek treatment from the subject’s primary healthcare provider(s) during study enrollment. There are no special considerations for biological data collected by the Quest system, as no biological material will be stored, collected, or analyzed at the University of Miami laboratory. Safety monitoring will include carefully assessing and promptly reporting all adverse events to the appropriate IRBs and Privacy Boards. Medical monitoring will include a regular assessment of the number and type of serious adverse events.

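### The weekly check-in is described as covering fatigue, motivation and adverse effects only in the combined arm, so non-serious harm and burden may be ascertained differently by arm

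*Protocol article*

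**What the plan says.** The weekly contact is described once for each arm.

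- **Exercise-only** (Interventional group 1, Adherence and engagement): calls of 10–15 minutes by phone or teleconference, which "will be conducted and documented to ensure protocol adherence, troubleshoot technical issues, and maintain engagement".
- **Sleep-only** (Interventional group 2, Missing data and adherence): calls of the same length, which "will be made to monitor engagement, support adherence, and troubleshoot technical issues".
- **Combined** (Interventional group 3, Protocol structure and considerations): "Weekly adherence and well-being check-ins will be conducted and documented to monitor fatigue, motivation, and adverse effects".

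The Data and safety monitoring plan applies to the whole trial. It says that "a medical doctor will monitor participants who report experiencing medical issues", that "Safety monitoring will include carefully assessing and promptly reporting all adverse events to the appropriate IRBs and Privacy Boards", and that "Medical monitoring will include a regular assessment of the number and type of serious adverse events". It does not say how adverse events are elicited from participants.

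The introduction to Interventional group 3 gives the assessment of participant burden as one purpose of that arm, to inform later multimodal work. The Analysis plan lists neither harm nor burden among its primary, secondary or tertiary outcomes.

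**The concern.** How many non-serious events and complaints of fatigue are recorded depends on whether participants are asked. Here the described asking varies with the randomized arm. Staff who followed the text would raise fatigue, motivation and adverse effects every week with 20 participants, and would hold a call about adherence and equipment with the other 40.

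Two kinds of statement are exposed. One is any by-arm description of adverse events. The other is any statement that combining the interventions adds burden, because that needs the single-intervention arms as a reference measured in the same way. Participants know their intervention and there is no sham (Interventional group 2, Limitations), so unequal questioning would add to a reporting risk that already exists.

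**Working it through.** The protocol gives no figure on this point to reproduce. The check is a comparison of texts, followed by an illustration of scale.

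**Step 1: set the sections side by side.**

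| | Exercise-only | Sleep-only | Combined |
|---|---|---|---|
| Weekly staff contact | yes | yes | yes |
| Adherence named | yes | yes | yes |
| Engagement or motivation named | engagement | engagement | motivation |
| Technical issues named | yes | yes | no |
| Fatigue named | no | no | yes |
| Adverse effects named | no | no | yes |
| Supervised sessions per week | 2 | none | 2 |

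The combined-arm section refers back to the exercise-only arm for the sessions and the cognitive tests. For the check-in it gives its own list. The two exercise arms give staff the same opportunity to observe problems in person, so between them the described difference lies in the call. Sleep-only has neither the supervised sessions nor the named questions, so its contrast with the combined arm is probably the largest.

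**Step 2: see whether the trial-wide safety section equalises this.** It promises that all adverse events are assessed, but states no method of asking. The only route that it describes to the doctor is a report by the participant. It neither says nor rules out that participants in the single-intervention arms are asked.

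**Step 3: scale, under assumptions.** The inputs are 20 participants per arm (Participant recruitment) and α = 0.05 (Analysis plan). The true event rates and capture probabilities are assumptions; the document gives none.

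Recorded proportion = true proportion × capture probability. The true proportion is set equal in all arms. Capture is 0.9 when asked and 0.6 down to 0.3 when not.

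| True proportion | Recorded, asked | Recorded, not asked | Difference (points) | Expected of 20 | Ratio |
|---|---|---|---|---|---|
| 20% | 18% | 12% to 6% | 6 to 12 | 3.6 v 2.4 to 1.2 | 1.5 to 3.0 |
| 30% | 27% | 18% to 9% | 9 to 18 | 5.4 v 3.6 to 1.8 | 1.5 to 3.0 |
| 40% | 36% | 24% to 12% | 12 to 24 | 7.2 v 4.8 to 2.4 | 1.5 to 3.0 |

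The true rate cancels from the ratio: 0.9 / 0.6 = 1.5 and 0.9 / 0.3 = 3.0. The ratio is therefore only the assumed capture ratio restated. A second set of assumptions (30% true rate, full capture when asked, 30–70% when not) gives 6 of 20 against 1.8 to 4.2 of 20, a ratio of 6 / 4.2 = 1.4 to 6 / 1.8 = 3.3.

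For reference only, since no such test is planned: exact enumeration of a two-sided Fisher test at 0.05, 20 against 20, gives a spurious significant result with probability about 4% to 32% across the table. With equal capture of 0.9 in both arms the ratio is 1.0 and that probability is about 2% to 2.5%.

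**The case against.** The strongest reply is that this is a condensed journal article. Scripts and forms for eliciting adverse events usually sit in the full protocol or a manual, and the listed call purposes need not be exhaustive. The safety section covers every arm, and an answer given during a weekly call is also a report. The fuller wording for the combined arm appears in a paragraph about managing cumulative burden and may be drafting rather than design. No between-arm analysis of harm or burden is listed.

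Most of this stands, and it rules out stronger readings:

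- **That the single-intervention arms rely on unprompted reports, or that none of their 40 × 8 = 320 weekly contacts asks about harm.** This is inferred from silence. No section says that adverse events go unasked in those arms.
- **That any comparison of harm between arms is biased.** Serious events are reviewed in all arms and depend less on prompting. Both exercise arms have the same supervised sessions.
- **That the combined arm will show about twice the events.** Such a figure restates an assumed 50% capture and is not a result from the document.

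The reply does not remove the discrepancy itself. The article does not merely omit the content of the check-in: it states that content for each arm, and states it differently. If practice is already uniform, the text still misdescribes it.

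**Conclusion.** The point holds as a discrepancy between the three arm sections that the safety section does not resolve. If the text is followed, non-serious adverse events and fatigue would tend to be recorded more completely in the combined arm, probably most clearly relative to sleep-only. The exposure is limited to descriptive statements on harm and on the added burden of combining; no listed outcome analysis is affected.

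The size cannot be derived from the document. Under the assumptions shown, the distortion is a ratio of about 1.5 to 3.0, or about 1 to 5 extra participants with an event out of 20 (0.06 × 20 = 1.2 to 0.24 × 20 = 4.8). If capture is in fact equal, there is none. The change is worth making because it is nearly free, not because a planned result depends on it.

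**What to change.** Reconcile the check-in descriptions in Adherence and engagement (group 1), Missing data and adherence (group 2), and Protocol structure and considerations (group 3) with the Data and safety monitoring plan. Use one check-in form, with the same fatigue, motivation and adverse-effect questions, at the existing weekly contact in all three arms. Base any by-arm description of adverse events and burden on that common form. Do this before data collection, because answers to questions that were not asked cannot be recovered later.

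The cost is a few sentences and one shared form, perhaps a minute or two more per call, and more minor events recorded in the single-intervention arms. No new visits or calls are needed.

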#### Cognitive pulse assessments

As in the other arms, participants will complete brief, digital cognitive assessments biweekly during lab visits and full-length assessments at week 0 and week 8. For improved standardization, participants in this group will also be asked to attend in-person exercise sessions on the days after they wore the Elemind Neuromodulation headband the preceding night.

#### Biomarker collection strategy

Biomarker collection through Quest Diagnostics (venipuncture at week 0 and week 8) will be conducted following the aforementioned procedures, with attention to minimizing scheduling conflicts with intervention activities. Just as in the exercise-only intervention, pre-intervention blood draws for this arm will occur no sooner than 24 hours before but no later than 7 days prior to commencing with the initial exercise session. Additionally, post-intervention blood draws will be obtained within 24–48 hours after completion of the final exercise session. No blood draws will occur on the same day as a scheduled exercise session.

#### Analysis strategy

This arm enables a unique opportunity to assess both the independent and combined contributions of sleep and exercise to cognitive, brain, and cardiometabolic outcomes. Statistical models will include main effects for sleep (e.g., adherence to Elemind usage), exercise (e.g., PGE, NPA), and interaction terms to evaluate additive or synergistic effects. Dose-response relationships will be explored using adherence metrics and physiological markers (e.g., heart rate during exercise, sleep efficiency). Adherence to both modalities will be assessed as previously described, summarized descriptively, and modeled as predictors in multivariable analyses of primary outcomes.

#### Compensation and parking reimbursement

All participants will receive $50 at baseline (week 0) and $50 at the conclusion (week 8) visit, totaling up to $100 for full participation in the trial. Participants will be issued a reloadable debit card (ClinCard) that can be used for study-based compensation at the University of Miami. Funds will be loaded onto the card according to the payment schedule. The study staff will provide information about how the card works. The company administering the card will require a full name, address, and date of birth to be entered online for payment. This information will only be used for payment and communication purposes and will not be given to another company or linked to any of the study data. All prospective participants who pass pre-screening eligibility but are found to be ineligible after the initial 7-day onboarding screening period and are also not eligible for or interested in being reassigned to an alternative intervention group for which they may be eligible will not be invited for further participation but will receive $20 compensation for their efforts via a ClinCard debit card. Furthermore, for all in-person visits, participants will be reimbursed for either parking or via Metro passes at the conclusion of each in-person visit.

### Measures and instruments

To capture a comprehensive and multidimensional view of participants’ cognitive, emotional, behavioral, and physiological profiles, the study will employ both survey-based instruments and digital device-based measures. Instruments will be categorized into predictor and outcome variables and will span psychosocial, cognitive, behavioral, and biological domains.

Self-report surveys will be administered at baseline (week 0) and at the 8-week follow-up by a trained research assistant or postdoctoral scholar via in-person visits or, if unable to come in person in the sleep-only group, by a secure video conference. These will include the PASE [22] and CHAMPS [23] questionnaires to assess physical activity and weekly caloric expenditure, respectively, for those in the exercise-only or sleep + exercise interventions. Additionally, each participant will complete all validated Patient-Reported Outcomes Measurement Information System (PROMIS) short-form questionnaires that measure sleep disturbance, self-reported cognitive functioning, emotional support, depression, anxiety, life satisfaction, and social isolation [21] at the baseline and post-intervention visits, except for the General PROMIS Life Satisfaction 5a questionnaire, which will be completed at the baseline visit only. Additional measures will include a Demographic Questionnaire, a Chronic Health Questionnaire, and the Cross Ethnic-Racial Identity Scale [44] to capture relevant sociodemographic and psychosocial predictors (see Table 3). Objective data will be collected via digital devices, including the Elemind Neuromodulation headband (sleep metrics), Fitbit Charge 5 (physical activity and heart rate), Lys sensor (light exposure), and the Digital Neuro-Signatures neuropsychological assessment (cognitive function). Blood-based biomarkers will be obtained through Quest Diagnostics to assess brain and cardiometabolic health for all participants at the baseline and post-intervention visits as well as AD-associated neuropathology for all participants at the baseline visit. The 6MWT will be used to assess changes in fitness and aerobic capacity. Together, these tools will enable high-resolution modeling of the relationships between behavior, biology, and cognitive health across all three study arms.

#### Physical Activity Scale for the Elderly (PASE) questionnaire

The PASE Questionnaire will only be administered to participants assigned to interventions involving exercise. The PASE is a validated, self-report instrument that is widely used to assess physical activity. The PASE Questionnaire was originally designated for community-dwelling adults aged ≥ 65 years but has been subsequently validated in adults aged 45–64 years [45]; this questionnaire has demonstrated high test-retest reliability, with intraclass correlation coefficients (ICC) found to be *r* = 0.75 (95% CI = 0.69–0.80) over 3–7 weeks [22]. Short-interval reliability (10–14 days) has shown excellent reproducibility with ICCs, which range from 0.93–0.99 in prior work [46, 47]. Furthermore, construct validity is moderately supported: correlations with accelerometer-measured physical activity (steps, energy expenditure) range from *r* ≈ 0.30–0.61 [48]. While internal consistency varies across activity domains (α ≈ 0.69–0.99 [22, 46]), the total score remains robust for classifying overall activity levels in older populations. Given the robustness of the PASE questionnaire across older adult populations, similar reliability is expected in upper middle-aged adults (55–64 years).

#### Community Healthy Activities Model Program for Seniors (CHAMPS) questionnaire

Similarly to the PASE questionnaire, the CHAMPS questionnaire will also be administered only to participants assigned to interventions involving exercise. The CHAMPS questionnaire is a validated, self-reported instrument that was originally designed to evaluate the effectiveness of an exercise intervention in community-dwelling older adults aged ≥ 65 years but has subsequently been demonstrated to be a valid tool to utilize for middle-aged participants as well [49, 50]. From the CHAMPS questionnaire, a Metabolic Equivalent of Task (CHAMPS–MET) metric can be derived. The CHAMPS-MET metric will be utilized to estimate weekly caloric expenditure [23]. The CHAMPS questionnaire has demonstrated acceptable construct validity and reliability in older adult cohorts, with reported correlations of *r* ≈ 0.23–0.55 when compared with accelerometer-based measures or functional health indicators [23, 49]. The CHAMPS questionnaire effectively captures activities typical of older adults’ daily routines and complements objective, wearable metrics.

